[figure not shown]

## 2. INTRODUCTION

During 2008, it is estimated that there were over 1.4 million new cases of cancers in the United States and over 500,000 lives were claimed. Worldwide, cancer of all types accounts for 3.5 million deaths annually. Treatment of neoplastic diseases represents an unsatisfied medical need worldwide.

Tumor treatment with radioactive isotopes has been used as a fundamental cancer therapy for decades. Selective delivery of effective doses of radioactive isotopes that destroy tumor tissue, spare surrounding normal tissue, do not accumulate in and damage vital organs (especially bone marrow, liver and kidneys), and that can be rapidly eliminated from the body remains a goal of targeted radiotherapies. Collectar has developed a novel radioiodinated therapy compound which takes advantage of the unique chemistry of phospholipid ethers (PLEs) and their analogs. Collectar's novel compound (CLR1404) is radiolabeled with the isotope iodine-131 (I-131).

Radiolabeled CLR1404 has been evaluated in both xenograft and spontaneous (transgenic) tumor models in mice and rats. Overall, these studies demonstrated specific uptake and retention in 40 + malignant tumor models. Anti-tumor activity has been demonstrated in nine tumor models (breast, prostate, lung, glioma, ovarian, renal, colorectal, pancreatic and melanoma) in mice, in which I-131-CLR1404 caused profound effects on tumor growth, thereby confirming radiolabeled CLR1404 as a potential anti-cancer therapeutic agent.

Toxicology and safety pharmacology studies in rodents and monkeys have demonstrated that non-radiolabeled ("cold") CLR1404 is well tolerated at doses up to 4.0 mg/kg, approximately 1000X the anticipated human dose (assuming 0.30 mg total dose injected into a 70 kg adult) with no significant adverse effects.

## 3. RATIONALE FOR THE STUDY

I-131-CLR1404 is a small-molecule, phospholipid ether analog that combines lipid-like properties with a cancer therapeutic beta-emitting radioisotope. Collectar believes that this compound will benefit individuals with cancer due to its selective retention and accumulation in malignant cells versus nonmalignant cells. Nonclinical experiments have demonstrated that I-131-CLR1404 significantly slows malignant tumor growth in several mouse tumor models. Survival studies with I-131-CLR1404 were conducted in glioma, ovarian, renal, colorectal and pancreatic tumor models and had significant effect on overall survival. Non-radiolabeled CLR1404 has been demonstrated to be safe in rodents, non-rodent, and nonhuman primate species at presumed therapeutic doses up to approximately 1000x the anticipated human dose.

Given this promising preclinical evaluation, Collectar is planning to evaluate I-131-CLR1404 in the clinical setting in patients with advanced cancers.

The primary objectives of the study will be dosimetry calculations and the determination of the millicurie dose which is expected to deliver 35-40cGy of radiation to bone marrow. This dose will be used as the starting dose in a subsequent maximum tolerated dose (MTD) study. The secondary objectives of the study will be to determine the safety profile and determine the pharmacokinetic profile of I-131-CLR1404.

I-131-CLR1404 is supplied as a ready-for-use radiopharmaceutical for intravenous dosing that is provided as a clear, faint yellow to yellow, sterile solution consisting of I-131-CLR1404 (18-(*p*-[I]-iodophenyl)octadecyl phosphocholine) and CLR1401 (18-(*para*-iodophenyl)octadecyl phosphocholine) in sodium chloride injection USP, ethanol USP/NF, polysorbate 20 NF, and sodium ascorbate USP. The study drug is packaged in a single-use glass vial and must be withdrawn through a 25mm, 0.22 or 0.45 micron sterile filter prior to administration. **The drug as supplied must be diluted to 10 mL with normal saline solution (normal saline for injection) and thoroughly mixed prior to administration via slow IV infusion.**

I-131-CLR1404 will be administered intravenously as a single dose infusion.

#### 4. STUDY OBJECTIVES

##### 4.1 PRIMARY OBJECTIVES

The primary objectives of the study are:

- To calculate whole body and organ radiation dosimetry of I-131-CLR1404
- To determine the millicurie (mCi) dose which is expected to deliver 35-40 centigray (cGy) of radiation to bone marrow, which will serve as a starting dose in a subsequent MTD study

##### 4.2 SECONDARY OBJECTIVES

The secondary objectives of the study are:

- To determine the safety of I-131-CLR1404
- To determine the pharmacokinetic profile of I-131-CLR1404

## 5. STUDY DESIGN

### 5.1 STUDY SUMMARY

This will be a multi-center study evaluating dosimetry and safety for up to nine patients with refractory or relapsed advanced solid tumors who have failed standard therapy or for whom no standard therapy exists. Patients who are eligible will be infused with a single dose of 10 millicuries (mCi) of I-131-CLR1404. All patients will be prescribed thyroid protection medication to be taken 24 hours prior to injection of the study drug and for 14 days afterwards.

**Patients who withdraw from the study prematurely will be strongly encouraged to continue their thyroid protective medication for the full 14 days post infusion.**

Whole body imaging for dosimetry calculations will be performed at 15-35 minutes post injection; 4-6, 18-24, 48, 72, and 144 hours (Day 6) post injection, and on Day 14 post injection. At the Investigator's discretion, optional SPECT imaging may be obtained between Day 3 and 14 to further characterize the patient's tumor(s). Blood and urine will be collected for clinical laboratory evaluation pre-dose and on days 6, 14, 30 and 42. Blood will be drawn for evaluation of lipids pre-dose and at 72 hours post injection. Blood will be collected for pharmacokinetic analysis prior to dosing, and at 5, 15, 30, and 60 minutes; 4-6, 18-24, 48, and 72 hours; 6, 14, 30, and 42 days post infusion. Blood will be collected for radiologic biodistribution at pre-injection, 15 and 60 minutes, 4-6, 18-24, 48, and 72 hours; 6, 14, 30 and 42 days post dose. Patients will be asked to collect all of their urine for 14 days post injection in order to evaluate the urinary clearance of I-131-CLR1404. Patients will be monitored at each visit for adverse events and the use of concomitant medications.

Patients must have a refractory or relapsed advanced solid tumor and have a sufficient window of time to complete the washout period of 2 weeks if they have received standard therapy or 4 weeks if they have received experimental therapy, the dosimetry data acquisition (14 days), and the follow-up safety assessment period (4 weeks) prior to beginning another cycle of a therapeutic regimen. If, after 30 days on study the patient is not experiencing any drug-related toxicity, the patient can continue further treatment with a clinically appropriate non-investigational therapy, at the discretion of the Investigator.

**Figure 5.1 Study Design**

[figure not shown]

After all patients have completed the protocol, calculations will be performed using OLINDA-generated biodistribution curves to predict the injected dose of I-131-CLR1404 in mCi/m^2 that will deliver a radiation absorbed dose of 35-40cGy to total bone marrow. This OLINDA-calculated dose will be considered the starting dose for a subsequent Phase 1 maximum tolerated dose protocol.

## 5.2 NUMBER OF CLINICAL SITES

Approximately four clinical sites in the United States may participate in the study.

## 6. PATIENT SELECTION

### 6.1 NUMBER OF PATIENTS

Up to nine patients are expected to be enrolled.

### 6.2 RECRUITMENT METHODS

The methods used for recruitment of patients in the study will be devoid of any procedures that may be construed as coercive. The recruitment process will not involve any restrictions on sociodemographic factors including gender or ethnic characteristics of the patient population. However, the composition of the study patient population will depend on patient sources available to the clinical site.

Patients will be recruited through an existing database of oncology patients, clinic contacts, and referring physicians. Anticipated recruitment rate is approximately four patients per month.

### 6.3 INCLUSION CRITERIA

Patients may be enrolled into this protocol only if all of the following inclusion criteria are met:

- Patients must have relapsed or refractory advanced solid tumor and have exhausted standard treatment options or no standard therapy exists for the patient.
- Patients must have a sufficient window of time to complete the washout period of 2 weeks if patients have received standard therapy or 4 weeks if patients have received experimental therapy, dosimetry data acquisition,(14 days), and the follow up safety assessment period (4 weeks) prior to beginning another cycle of a therapeutic regimen.
- Patient is ambulatory with an ECOG performance status of 0 or 1 (Appendix C), and an estimated life expectancy of  $\geq 4$  months.
- Patient is 18 years or older
- Patient is judged by the Investigator to have the initiative and means to be compliant with the protocol and be within geographical proximity to make the required study visits.
- Patients or their legal representatives must have the ability to read, understand and provide written informed consent for the initiation of any study related procedures.
- Patients with brain metastasis are acceptable if the clinical condition has been stable for at least one month. For patients with brain metastasis or glioblastoma multiforme who require steroids, they must have been on a stable or tapering dose of corticosteroids for at least one month.
- Female patients of childbearing potential must have a negative serum pregnancy test within 24 hours of start of treatment.
- Patients must agree to use an effective method of contraception (e.g., oral contraceptives, double-barrier methods such as a condom and a diaphragm, intrauterine device, Norplant, Depo-Provera) during the study and for 90 days following the last dose of study medication.

### 6.4 EXCLUSION CRITERIA

Patients will be excluded from enrollment if any of the following apply:

- Patient or physician plans concomitant chemotherapy, therapeutic radiation treatment, and/or biological treatment for cancer including immunotherapy while on study. Of note, localized palliative radiation therapy for bone pain will be allowed during the study period if clinically indicated. Ongoing hormonal therapy may be continued.
- Patients who have had more than 25% of the total bone marrow irradiated.
- Patients with diffuse lung disease or interstitial spread of carcinoma.
- Patients in whom the bladder or rectum is within a prior radiation therapy field and a dose of greater than 45 Gy was administered.
- Patients with total therapeutic radiation dose in excess of 25 Gy to the kidney, 45 Gy to brain, 45 Gy to stomach, 18 Gy to lung, or 25 Gy to liver.
- Patients receiving prior total-body irradiation.

- Patients with extradural tumor in contact with the spinal cord, or tumor located where swelling in response to therapy may impinge upon the spinal cord.
- Prior radiation therapy or chemotherapy within 2 weeks of the start of the study. Of note, patients on biologics such as cetuximab (Erbix®) are acceptable if the patient has completed a washout phase. (Washout is one half-life of the drug or 2 weeks, whichever is longest).
- Patient has another active medical condition(s) or organ disease(s) that may either compromise patient safety or interfere with the safety and/or outcome evaluation of the study drug.
- While this exclusion is not limited to the following abnormalities, if any of the following laboratory abnormalities are present, the patient should be excluded:
  - WBC < 3000/ $\mu$ L
  - Absolute neutrophil count < 1500/ $\mu$ L
  - Platelets < 150,000/ $\mu$ L
  - Hemoglobin  $\leq$  11.0 gm/dL
  - Total bilirubin > 1.5 x upper limit of normal for age
  - SGOT or SGPT > 3 x upper limit of normal for age if no liver metastases or >5 x upper limit of normal for age in the presence of liver metastases
  - Serum creatinine > 1.5 x upper limit of normal for age
  - INR  $\geq$  2.0
- Patient has been treated with an investigational drug, investigational biologic, or investigational therapeutic device within 30 days of initiating study treatment.
- Patients who have received severely marrow toxic drugs (e.g. nitrosoureas, mitomycin).
- Patients who have received prior treatment with Iodine-131 in the past five years.
- Patients receiving concurrent hemodialysis.
- Patients receiving blood transfusions within 60 days of study start.
- Patients receiving hematopoietic growth factor therapy within 60 days of study start.
- Patients receiving prior stem cell transplantation.
- Patients with clinically evident ascites or with peritoneal carcinomatosis.
- Patient has clinically significant cardiac co-morbidities including: congestive heart failure (New York Heart Association class III-IV heart disease), a LVEF < 40%, unstable angina pectoris, serious cardiac arrhythmia requiring medication or a pacemaker, myocardial infarction within the past six months.
- Patient has clinically significant pulmonary impairment defined as an SaO2 on room air of 93% or less.
- Concurrent or recent (within 1 month) use of thrombolytic agents, or full-dose anticoagulants (except to maintain patency of preexisting, permanent indwelling IV catheters). Of note, therapy with low-molecular weight heparin is acceptable as long as the INR < 2.0.

- Patients with uncontrolled hypertension as defined by SBP > 150 mm/Hg, DBP > 100 mm/Hg or patients with uncontrolled diabetes that would compromise patient safety or interfere with the safety and/or outcome evaluation of the study drug.
- Grade II-IV peripheral vascular disease or has had peripheral vascular surgery within the past year
- Less than 4 weeks since prior major surgery
- Known positive for HIV, Hepatitis C (active, previously treated or both), or is Hepatitis B core antigen positive
- Concurrent chronic use of aspirin (325 mg/day or more)
- Patient is pregnant or lactating.
- Patients with colostomy/ileostomy.
- Patients with poor venous access who will be unable to receive study drug into a peripheral venous catheter
- Prior allergic reactions to iodine, or other study agents
- Significant traumatic injury within the past 4 weeks
- Ongoing or active infection requiring antibiotics or with a fever >38.1°C (>101° F) within 3 days of the first scheduled day of dosing
- Patients who are hospitalized.

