#### 9.4 GRADING AND RELATEDNESS OF ADVERSE EVENTS

##### 9.4.1 Grading of Severity of an Adverse Event

The severity of each adverse event will be graded as mild, moderate, severe, life threatening, or death which corresponds to Grades 1, 2, 3, 4 and 5, respectively on the National Cancer Institute Common Toxicity Criteria for Adverse Events (NCI CTCAE) version 3.0. These criteria must be used in grading the severity of adverse events. The criteria can be found at: [www.fda.gov/cder/cancer/toxicityframe.htm](http://www.fda.gov/cder/cancer/toxicityframe.htm).

For those adverse events which are not listed as part of the NCI CTC, the same grading system should be used, where:

**Grade 1:**        **Mild** corresponds to an event not resulting in disability or incapacity and which resolves without intervention;

**Grade 2:**        **Moderate** corresponds to an event not resulting in disability or incapacity but which requires intervention;

**Grade 3:**      **Severe** corresponds to an event resulting in temporary disability or incapacity and which requires intervention;

**Grade 4:**      **Life-threatening** corresponds to an event in which the patient was at risk of death at the time of the event;

**Grade 5:**      **Fatal** corresponds to an event that results in the death of the patient.

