### *10.2 DOSE LIMITING CRITERIA*

In general, Dose Limiting Toxicities (DLTs) will be considered as toxicities that are related to treatment with I-131-CLR1404 and that are:

1. Hematological
  - a. Any CTCAE Grade 4 toxicity (except Grade 4 neutropenia without concurrent fever which must be present for  $\geq 7$  days to constitute a DLT)
  - b. CTCAE Grade 3 neutropenia with fever
  - c. CTCAE Grade 3 thrombocytopenia associated with bleeding
2. Non-Hematological
  - a. Any CTCAE Grade 3 toxicity despite adequate supportive care (supportive care limited to nausea, vomiting and diarrhea only)
  - b. Any CTCAE Grade 4 toxicity

If 2 patients experience a DLT, study enrollment will be stopped pending discussions with the Principal Investigator, Collectar Medical Monitor and the Agency.

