#### *11.3 SAMPLE SIZE*

As there is little information on the effect of I-131-CLR1404, this study is meant to be hypothesis generating and no formal sample size calculation will be performed.

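### The fever exclusion in section 6.4 gives one limit as two unequal temperatures: 38.1°C is 100.6°F, and 101°F is 38.3°C

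*Protocol*

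**What the plan says.** The list in Protocol section 6.4 excludes a patient if any single item applies. One item concerns infection: "Ongoing or active infection requiring antibiotics or with a fever" above a stated limit. The full fever limb reads "with a fever >38.1°C (>101° F) within 3 days of the first scheduled day of dosing". The Celsius figure comes first, to one decimal. The Fahrenheit figure follows in parentheses as a whole number. Both carry a strict greater-than sign.

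Temperature is recorded at screening and again before the infusion on Day 0 (sections 8.2.1, 8.2.2 and 8.2.3.6). None of those sections fixes a unit. Section 5.2 foresees about four US sites, and section 6.1 allows up to nine patients.

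**The concern.** A parenthetical figure in a second unit is normally read as the same limit, so that a site may use either. That works only if the two agree. Here a reading can lie above one figure and not above the other, and nothing in section 6.4 says which prevails.

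What is at stake is consistent eligibility. Two sites could classify the same infected patient differently, and a monitor checking compliance would have no basis in the text for calling either decision a deviation.

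**Working it through.** **Inputs.** Both come from the fever limb of section 6.4: a limit above 38.1°C, and a limit above 101°F.

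**Formulas.** F = C × 9/5 + 32 and C = (F − 32) × 5/9.

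**Can the stated pair be reproduced?**

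- Celsius to Fahrenheit: 38.1 × 9/5 + 32 = 68.58 + 32 = 100.58°F, or 100.6°F at one decimal. It becomes 101 only when rounded up to a whole degree.
- Fahrenheit to Celsius: (101 − 32) × 5/9 = 69 × 5/9 = 38.33°C, or 38.3°C at the one-decimal precision that the criterion uses. It does not return 38.1.
- Gap: 38.33 − 38.10 = 0.23°C, and 101 − 100.58 = 0.42°F.

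So the pair is reproduced in one direction only, and only with whole-degree rounding.

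**Which readings are affected?** Applying each strict limit as printed:

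| Reading | Converted | Above 38.1°C? | Above 101°F? |
|---|---|---|---|
| 38.1°C | 100.58°F | No | No |
| 38.2°C | 100.76°F | Yes | No |
| 38.3°C | 100.94°F | Yes | No |
| 38.4°C | 101.12°F | Yes | Yes |

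On a Fahrenheit thermometer reading to one decimal, 100.5°F (38.06°C) is above neither limit. Readings from 100.6°F (38.11°C) to 101.0°F (38.33°C) are above the Celsius limit only, and 101.1°F (38.39°C) is above both. The disputed band is therefore 38.2 to 38.3°C, or 100.6 to 101.0°F.

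**Which patients are affected?** The fever limb is one of two alternatives within an infection criterion.

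- Infection requiring antibiotics: excluded through the first limb, so the mismatch is irrelevant.
- Infection not requiring antibiotics, reading in the band: excluded by the Celsius figure and not by the Fahrenheit figure. This is the conflict.
- Fever without infection, reading in the band: affected only if the item is read loosely, with fever standing alone as a reason for exclusion.

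**The case against.** The strongest reply is that this is loose rounding and not two rules. The Celsius figure leads and carries a decimal, the Fahrenheit figure is in parentheses without one, and 100.58 rounds to 101. Since both are printed side by side, a site could treat Celsius as governing. That plausibly explains how the mismatch arose, but it does not remove it. Whole-degree rounding turns every one-decimal Celsius value from 38.1 (100.58°F) to 38.6 (101.48°F) into 101°F, so the rounded figure cannot stand in for the Celsius one. Nor does the protocol say that Celsius governs.

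A second reply is that hardly anyone is affected. Infections needing antibiotics are excluded anyway, and some remaining patients may be caught by other items in section 6.4, such as the one on another active medical condition or the one on hospitalization. This stands, and it limits the size of the point.

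A reader might go further and link the mismatch to the dose-limiting toxicities in section 10.2. Two of those turn on fever: "CTCAE Grade 3 neutropenia with fever", and the exception for Grade 4 neutropenia "except Grade 4 neutropenia without concurrent fever". The rule "If 2 patients experience a DLT, study enrollment will be stopped pending discussions" then depends on the count. The documents do not support that link. The section 6.4 figure is an entry criterion for the days before dosing. Section 10.2 concerns toxicity after it, gives no temperature, and neither cites nor borrows the entry limit. Its toxicities are expressed in CTCAE grades, and of CTCAE version 3.0 section 9.4.1 says "These criteria must be used in grading the severity of adverse events". Whether that standard supplies a fever figure cannot be checked from the protocol. The silence of section 10.2 on temperature is not caused by the conversion error, and correcting section 6.4 would not change it.

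**Conclusion.** The criterion is wrong as written, and the error is minor. One exclusion limit is given as two temperatures that differ by 0.23°C (0.42°F). An actively infected patient who needs no antibiotics and has a reading above 38.1°C but not above 101°F is excluded by one figure and not by the other.

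The unit conversion needs no assumptions. The narrow reach rests on reading the fever limb as part of the infection item, which is its natural reading; a looser reading adds patients with fever and no infection. Either way it concerns a small group among at most nine patients. The protocol gives no basis for estimating how many would have a reading in the band. The dosimetry and marrow-dose calculations do not use the figure, and the study has no sample size calculation that it could affect: section 11.3 states that "no formal sample size calculation will be performed". The conclusion covers entry only and says nothing about how toxicities are counted or when enrollment pauses.

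**What to change.** Reconcile the two figures in section 6.4 so that they are the same temperature, shown in both units to the same precision (for example, one decimal in each). The sponsor's clinicians should choose the value. This review proposes none, and the documents do not show which of the two was intended. Section 10.2 needs no change on account of this point.

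The cost is one line of protocol text. Because the line is an eligibility criterion, the sponsor should decide under section 12.3 whether the correction counts as administrative or goes to the IRB, where it could travel with another amendment. No procedure, visit or analysis changes. The only effect on conduct is that readings in the disputed band would be classified the same way at every site.

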## 7. STUDY DRUG ADMINISTRATION

### 7.1 DESCRIPTION OF STUDY DRUG

I-131-CLR1404 is supplied as a ready-for-use radiopharmaceutical for intravenous dosing that is provided as a clear, faint yellow to yellow, sterile solution consisting of I-131-CLR1404 (18-(*p*-[I]iodophenyl)octadecyl phosphocholine) and CLR1401 (18-(*para*-iodophenyl)octadecyl phosphocholine) in sodium chloride injection USP, ethanol USP/NF, polysorbate 20 NF, and sodium ascorbate USP. The study drug is packaged in a single-use glass vial and must be withdrawn through a 25 mm, 0.22 or 0.45 micron sterile filter prior to administration. **The appropriate volume of study drug sufficient to give a measured 10 mCi dose must then be diluted to 10 ml with normal saline solution (normal saline for injection) and thoroughly mixed prior to administration via slow IV infusion.**

I-131-CLR1404 is radioactive and should only be prepared, assayed, and administered by personnel who are licensed and trained to handle radioactive materials. Proper radiation shielding should be used during storage, preparation, assay, and administration of I-131-CLR1404. The study drug will arrive from Collectar in a lead shipping container, and should remain in the lead shipping container for storage, out of direct sunlight and at room temperature.

The physical half-life of iodine-131 is approximately 8.02 days. Iodine-131 decays with beta emissions of 334 keV (7.3%) and 606 keV (89.9%), and gamma emissions of 284.3 keV and 364.5 keV. The therapeutic radiation effects are primarily from beta emissions, while gamma emissions are useful for imaging.

